### Participant timeline {13}

According to the study protocol, patients must have undergone surgery for a chronic subdural hematoma within 24 h prior to study inclusion. In this context, the following steps must be carried out before inclusion in the study (Fig. 1). The schedule for participants from study entry is shown in Table 1.

**Fig. 1 Fig1:**
[figure not shown]
Steps that have to be carried out, before potential participations can be enrolled in the study

### Sample size {14}

In order to estimate the required sample size, the volume change of a primary operated CSDH under the adjuvant therapy forms to be investigated is analogized with the recurrence rates of primary operated and adjuvant embolized or adjuvant drug-treated CSDH in the literature with regard to the target value defined within the primary objective. For example, the MEMBRANE study, which is currently being recruited, assumes a recurrence rate of 10% when combined surgical and interventional therapy is used [11]. In comparison, the work of Hibahashi et al. [27] puts the recurrence rate of CSDH treated with a combination of surgery and medication at around 2%. Based on this, using the *z*-test for independent samples and an error of the first kind (*α* = 0.05), a sample size of 276 patients (138 per group) is required to achieve a power > 0.8 to detect a difference of 8%.

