**Methods:**

TABASCO is a prospective, randomized, two-arm, multicenter, clinical trial designed to determine whether postoperative treatment of chronic subdural hematomas using adjuvant drug therapy with tranexamic acid (test group) is equivalent to postoperative embolization of the arteria meningea media (control group) in terms of postoperative volume reduction of the hematoma and the need for revision surgery of CSDH. Patients over 18 years of age who have undergone surgery for CSDH for the first time no more than 24 h before inclusion in the study will be randomized 1:1 to the test group or control group. The primary endpoint is the postoperative volume decrease of a primarily surgically relieved CSDH quantitatively and regarding to the time course on the affected side in a study period of 3 months postoperatively. The secondary endpoint of this study is to investigate the extent to which the rate of necessary revision surgery can be influenced by the adjuvant therapy procedures over the course of 3 months. The tertiary endpoint is the neurological outcome of the patients included in the study and assigned to the different treatment arms after a total follow-up period of 3 months as well as the complication rate of the adjuvant procedures used. Assuming a risk difference of 8% for rebleeding and surgical revision, with an applied power of 80%, 276 patients (138 per group) will be included in this study.

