### Outcomes {12}

#### Primary outcome

The primary element to be investigated in this study is the postoperative volume development of a primarily surgically relieved unilateral CSDH over the course of 3 months postoperatively. For diagnostic purposes and documentation, cranial cross-sectional imaging using native cMRI or CT-scan and subsequent volumetry to visualize the residual hematoma volume in milliliters will be performed at the planned follow-up time points, 1 day postoperatively, 1 week postoperatively, 1 month postoperatively, 2 months postoperatively and 3 months postoperatively. The volumetry will be performed by a radiologist who is not involved in the study. Although he is not informed about the group assignment of each patient, he is not blinded because the group assignment can easily be identified from the radiological evidence of the embolism material in the imaging. All findings are considered in relation to each other and in relation to the initial findings before the operation. The planned examination intervals correspond to the current standard of care for postoperative imaging follow-up after CSDH surgery and reflect the procedure used in comparable studies [27].

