#### Secondary outcome

To answer the question specified in the secondary objective, the need for revision surgery on the primary side of patients included in the study is documented depending on the study arm as well as the time interval to the primary procedure.

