## Abbreviations

cMRI: Cranial magnetic resonance imaging
CSDH: Chronic subdural hematoma
CT: Computed tomography
EMA: European Medicines Agency
DKRS: German Clinical Trials Registry
DSA: Digital subtraction angiography
MMA: Middle meningeal artery
mRS: Modified Rankin Scale
MRI: Magnetic resonance imaging
NIHSS: The National Institutes of Health Stroke Scale
PI: Principal investigator
SAEs: Serious adverse events
SPSS: Statistical Package für Social Sciences (IBM®)
TABASCO: Tranexamic acid vs. embolization of the meningeal artery as an adjunctive therapeutic regime to reduce the recurrence rate after surgical relief of chronic subdural hematomas
TXA: Tranexamic acid

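### The 276 patients and the power above 0.8 are calculated for recurrence/revision, the secondary outcome; power for the primary volume endpoint is not established

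*Protocol article*

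**What the plan says.** The Abstract (Methods) defines the primary endpoint: "The primary endpoint is the postoperative volume decrease of a primarily surgically relieved CSDH quantitatively and regarding to the time course". Outcomes {12} agrees: "The primary element to be investigated in this study is the postoperative volume development of a primarily surgically relieved unilateral CSDH", measured by volumetry in ml at five postoperative times. Revision surgery is the secondary outcome: "the need for revision surgery on the primary side of patients included in the study is documented depending on the study arm".

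Sample size {14} refers to the target quantity of the primary objective, but says that volume change is "analogized with the recurrence rates of primary operated and adjuvant embolized or adjuvant drug-treated CSDH in the literature". Its two inputs are both recurrence rates. For embolization, the cited study "assumes a recurrence rate of 10% when combined surgical and interventional therapy is used". For tranexamic acid, the cited work "puts the recurrence rate of CSDH treated with a combination of surgery and medication at around 2" per cent. A z-test for independent samples at alpha 0.05 then gives 276 patients, 138 per group, with power above 0.8 for a difference of 8%. The Abstract describes the same 8% as a difference in the risk of rebleeding and revision surgery.

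Statistical methods {20a} compares volume between groups by t-test or Mann–Whitney U-test at each time point, and revision surgery by the Pearson chi-squared test.

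**The concern.** A sample size supports the endpoint whose effect and variability went into it. Here both inputs are proportions, and the test used for sizing is the counterpart of the chi-squared test planned for revision surgery. The primary endpoint is continuous and has a different test. The only bridge between the two is an analogy, and an analogy supplies neither a difference in ml nor an SD.

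Because Sample size {14} ties the calculation to the primary objective, a reader will take 276 patients as giving more than 80% power for volume. Nothing in the document supports that. At stake is the justification of the sample size for the endpoint on which the trial will be judged: the plan does not say what volume difference it can detect, or what margin it could exclude.

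**Working it through.** **Inputs.** From Sample size {14}: 10% (embolization), about 2% (tranexamic acid), alpha 0.05, power above 0.8, 138 per group. From Trial design {8}: 1:1 allocation. Sidedness is not stated; two-sided is assumed because it reproduces the figure.

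**Step 1: reproduce 138 per group.** Pooled two-proportion z-test, mean rate (0.10 + 0.02)/2 = 0.06:

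n = [1.96 × √(2 × 0.06 × 0.94) + 0.8416 × √(0.10 × 0.90 + 0.02 × 0.98)]² / 0.08²

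= [1.96 × 0.3359 + 0.8416 × 0.3311]² / 0.0064 = 0.9369² / 0.0064 = 137.2, so 138 per group and 276 in total.

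Power by the same formula is 0.7996 at 137 and 0.802 at 138, so 138 is the smallest group size above 0.80. The other variants do not match:

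| Variant | n per group |
|---|---|
| Two-sided, pooled | 138 |
| Two-sided, unpooled | 135 |
| Two-sided, arcsine | 122 |
| Two-sided, continuity correction | 162 |
| One-sided, pooled | 108 |
| One-sided, continuity correction | 132 |

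The exact power of the planned Pearson test at 138 per group is 0.839. The stated figure is therefore sound for 10% against 2%, and it comes wholly from those two rates.

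**Step 2: what 138 per group gives for volume.** The document gives no volume difference, SD or margin, so the result can only be expressed in SD units. For a two-sided difference test at one time point (an assumption), 80% power is reached at

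d = (1.96 + 0.8416) × √(2/138) = 2.8016 × 0.1204 = 0.337 (0.338 with the t distribution).

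For the Mann–Whitney test with normal data, 0.338 / √(3/π) = 0.346.

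Under the normal approximation:

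| Assumed difference (SD) | Power at 138 per group | n per group for 80% |
|---|---|---|
| 0.20 | 0.38 | 393 |
| 0.25 | 0.55 | 252 |
| 0.30 | 0.70 | 175 |
| 0.40 | 0.91 | 99 |
| 0.50 | 0.99 | 63 |

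**Step 3: illustration in ml.** If the SD of volume were 15 to 40 ml (an assumption; the document gives none), 0.338 SD would be 0.338 × 15 = 5.1 ml to 0.338 × 40 = 13.5 ml.

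**Step 4: if the question is equivalence.** The Abstract and Trial design {8} ask whether the treatments are equivalent. Power then depends on a margin in ml, which is not given. What 138 per group fixes is precision: the 95% confidence interval for the mean difference at one time point has half-width 1.96 × √(2/138) = 0.24 SD.

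**The case against.** The strongest reply is that the protocol is open about its method. It says that it argues by analogy, the Abstract labels the 8% as a risk difference, and no sentence states a power for a volume difference. The title's stated purpose, "as an adjunctive therapeutic regime to reduce the recurrence rate after surgical relief of chronic subdural hematomas", also makes recurrence a natural quantity to size on. This stands in part. A reader might infer that the protocol explicitly claims more than 80% power for volume; it does not. It implies as much, by placing the calculation under the primary objective. Disclosing an analogy does not supply the effect and variance that a power for volume needs.

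A second reply is that an article condenses the full protocol. That does not help here, because the basis given is complete and reproduces 276 exactly. Nothing has been left out; the basis is for another outcome.

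A third reply is that recurrence is not the same as revision surgery. The Abstract joins them when it defines the 8%, and on neither reading is the quantity a volume.

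A fourth reply is that 276 may be plenty for volume. That is correct: 0.34 SD is a modest detectable difference.

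**Conclusion.** The point holds as one about which outcome the power belongs to. The 276 patients and the power of 0.802 rest entirely on 10% against 2% recurrence/revision, the secondary outcome. Power for volume is not established: over assumed differences of 0.20 to 0.50 SD it runs from 0.38 to 0.99, for a two-sided difference test at a single time point with all 276 evaluable.

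Stronger readings that a reader might infer are not supported:

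- *The calculation is wrong.* It reproduces exactly.
- *The trial is underpowered for volume.* This cannot be shown without a volume difference and an SD, and the document gives neither.
- *A null volume result could not be interpreted.* It could be read from the confidence interval for the volume difference. The gap is in the planning justification.
- *Revision surgery should become the primary outcome.* The trial has been recruiting since May 2024 (Trial status), and such a switch is a debatable design choice that the mismatch does not compel.

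**What to change.** In the Abstract (Methods) and Sample size {14}, state that 276 evaluable patients give about 80% power for revision surgery at 10% against 2%, two-sided alpha 0.05, and that this power does not apply to the volume endpoint. Delete the analogy from Sample size {14}.

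Then state what 138 per arm delivers for volume, after settling which question is asked:

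- If it is a difference at a named time point: 80% power for about 0.34 SD (t-test) or 0.35 SD (Mann–Whitney), converted to ml from a stated and sourced SD.
- If it is equivalence, as the Abstract and Trial design {8} say: the expected precision, or the power against a stated margin in ml.

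Because the primary outcome is described as a time course, the statement should name the time point or summary to which it refers.

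The cost is a few sentences, handled by the amendment and registry route that the protocol already describes in section {25}. No additional patients are needed. The downside is that the stated figure becomes less favourable, since the trial can no longer be read as having 80% power for its primary endpoint unless a volume assumption supports it.

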### Criteria for discontinuing or modifying allocated interventions {11b}

Patients may withdraw their consent at any time without providing a reason and thus terminate their participation in the study prematurely. Withdrawal from the study and reasons, if known, will be documented. Study treatment stops if a surgical treatment for the CSDH is necessary during follow-up, in case of subsequent occurrence of an exclusion criterion or in occurrence of treatment-related complications during treatment. Crossover to the other study arm is not possible after the start of treatment in the respective study arm. Moreover, the principal investigator is entitled to terminate the study prematurely if new scientific findings in favor of one or the other treatment violate the equipoise principle.

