## Assignment of interventions: allocation

### Sequence generation {16a}, concealment mechanism {16b}, and implementation {16c}

After the neurosurgeon has checked the inclusion and exclusion criteria, the participants are assigned to treatment with tranexamic acid or embolization in a 1:1 ratio in each study center by means of block randomization after they have given their informed consent and the baseline data have been recorded.

If, in the course of the randomized group allocation, it will be apparent that there are exclusion criteria for inclusion in the test group in the sense of contraindications for the administration of tranexamic acid, or if it will be determine during the procedure that vascular anomalies prevent embolization in patients randomized to the control group, a crossover to the corresponding comparison group is possible after prior further clarification.

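### The power above 0.8 is the z-test power of 138 evaluable patients per group with no crossover, yet the same 276 is the number to be included

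*Protocol article*

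**What the plan says.** Sample size {14} rests on two recurrence rates. For embolization it cites a trial that "assumes a recurrence rate of 10% when combined surgical and interventional therapy is used"; for surgery plus medication it takes about 2% from another cited study. It then reports, "using the *z*-test for independent samples" and alpha 0.05, that "a sample size of 276 patients (138 per group) is required" for power above 0.8. The Abstract (Methods) repeats the number as the enrolment figure: "276 patients (138 per group) will be included in this study".

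Other sections provide for patients who will not contribute fully to that comparison:

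- Criteria for discontinuing {11b}: "Patients may withdraw their consent at any time without providing a reason".
- Section {20c} foresees missing data for primary endpoints and other analyses.
- Intervention description {11a} allows crossover to embolization for tranexamic acid contraindications, and crossover to tranexamic acid for a vascular variant that rules out embolization.
- Sequence generation {16a} covers both directions after randomised allocation: "a crossover to the corresponding comparison group is possible after prior further clarification".
- The exclusion criteria remove only patients who cannot have embolization in time and also have a contraindication to tranexamic acid. A patient with one of these obstacles can be randomised.

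**The concern.** A sample size formula returns the number of patients who must be evaluable and must carry the assumed event rate of their arm. When the formula's result is also the enrolment figure, nothing is left for withdrawal, missing outcomes or dilution by crossover. Because the article gives the same 276 as required and as included, no allowance in an unseen full protocol can sit between the two.

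At stake is how the stated power is read. It is the only power figure in the article, and readers will use it to judge how informative the revision comparison is. If some enrolled patients are lost or cross over, the power of the comparison is lower than that figure, by an amount the article lets nobody estimate.

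**Working it through.** **Inputs.** From Sample size {14}: p1 = 0.10 (embolization), p2 = 0.02 (tranexamic acid), alpha 0.05, z-test, power above 0.8. Sidedness is not stated; two-sided is the reading that reproduces the result. From Trial design {8}: 1:1 allocation. The documents give no rate for loss or crossover, so those below are assumed.

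**The plan's own figure.** With mean rate 0.06, the pooled z-test size per group is

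n = [1.96·√(2·0.06·0.94) + 0.8416·√(0.10·0.90 + 0.02·0.98)]² / 0.08² = [(0.6583 + 0.2786) / 0.08]² = 137.15, rounded up to 138.

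The stated figure is reproduced. Other common forms give a different number per group: unpooled 135, continuity-corrected 162, one-sided 108, arcsine 122. So 138 is the pooled two-sided result with no inflation.

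**Power at n per group.**

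Power = Φ{[|p1 − p2|·√n − 1.96·√(2·p̄·(1 − p̄))] / √(p1(1 − p1) + p2(1 − p2))}

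At n = 138: (0.9398 − 0.6583) / 0.3311 = 0.850, and Φ(0.850) = 0.802. At n = 137 it is 0.7996.

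**Exact power of the planned test.** Statistical methods {20a} plans the Pearson chi-squared test for revision surgery. Summing the two binomial distributions over all outcomes with |z| > 1.96 gives 0.839 at 138 per group. It is still 0.802 at 126 per group (12 of 138 lost, 8.7%) and falls to 0.798 at 125.

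**Loss and crossover.** Suppose a share c1 crosses from tranexamic acid to embolization and c2 crosses the other way. If they are analysed as randomised and take the other arm's rate:

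- p_TXA = 0.02(1 − c1) + 0.10·c1
- p_emb = 0.10(1 − c2) + 0.02·c2

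Loss of 5% leaves 131 per group (138 × 0.95 = 131.1); loss of 10% leaves 124 (138 × 0.90 = 124.2).

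| Loss | c1 | c2 | Rates compared | n per group | z-test | Exact Pearson |
|---|---|---|---|---|---|---|
| 0 | 0 | 0 | 2.0% v 10.0% | 138 | 0.802 | 0.839 |
| 5% | 0 | 0 | 2.0% v 10.0% | 131 | 0.782 | 0.818 |
| 10% | 0 | 0 | 2.0% v 10.0% | 124 | 0.759 | 0.795 |
| 0 | 2% | 0 | 2.16% v 10.0% | 138 | 0.781 | 0.816 |
| 0 | 5% | 0 | 2.4% v 10.0% | 138 | 0.747 | 0.778 |
| 5% | 5% | 0 | 2.4% v 10.0% | 131 | 0.725 | 0.755 |
| 10% | 10% | 5% | 2.8% v 9.6% | 124 | 0.604 | 0.620 |

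Over 5–10% loss, 5–10% crossover from tranexamic acid and 0–5% the other way, the z-test power therefore runs from about 0.60 to 0.73, and the exact power from about 0.62 to 0.755.

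**The case against.** The defence has several sound parts.

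- **The calculation is correct.** A reader might infer that 276 is a miscalculation. It is not; the gap is the missing allowance.
- **The planned test has slack.** A reader might infer that 138 per group reaches 0.80 only with complete follow-up and no crossover. For the Pearson test that is false: loss up to about 8.7%, or 2% crossover from tranexamic acid without loss, leaves exact power above 0.80.
- **Loss may be small.** Follow-up lasts three months, runs alongside routine outpatient care and is booked at discharge {18b}. Data already collected are kept unless consent to their processing is withdrawn {27}.
- **Crossover is bounded.** Tranexamic acid contraindications are to be checked at inclusion {11a}, and crossover is barred once treatment has started {11b}. Nothing in the documents supports a very high rate.
- **Dilution is conditional.** It arises only if patients are analysed as randomised. The article names no analysis population, which may properly be left to an analysis plan. An as-treated analysis would avoid the dilution but give up the randomised comparison. Crossed patients may also not have exactly the other arm's rate.

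All of this limits the claim without removing it. Section {16a} still provides for crossover after allocation, and 5% in one direction, with no loss at all, takes both the z-test (0.747) and the exact test (0.778) below 0.8.

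**Conclusion.** The point holds in a conditional form. The 276 is the uninflated z-test size and also the number to be included, so the stated power above 0.8 describes evaluable patients without crossover, not 276 enrolled patients under the protocol's own provisions. Loss alone is a minor matter. Crossover analysed as randomised is the main source of any shortfall, and under the assumed ranges z-test power is about 0.60 to 0.73.

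Two stronger readings are not supported. One is that the trial is shown to be underpowered: without documented rates that cannot be said. The other is that overstated power is what would let a non-significant result pass for equivalence. That risk comes from pairing an equivalence aim with difference tests; it would remain at full power and is a separate matter.

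All these figures concern recurrence or revision, the secondary outcome. The primary outcome is hematoma volume, which the Sample size section links to recurrence only by analogy, so nothing here measures power for it.

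**What to change.** In Sample size {14} and the Abstract:

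1. State that 138 per group is the evaluable number with no crossover, and that the z-test power of 0.80 applies to that case.
2. Report, by one named method, the power of 276 enrolled patients over a stated range of loss and crossover analysed as randomised. By z-test this is about 0.60–0.73 for 5–10% loss, 5–10% crossover from tranexamic acid and 0–5% the other way. Label the rates as assumptions, and do not mix z-test and exact values in one range.
3. State that this power concerns recurrence or revision.

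The change is wording only. It needs no extra patients and leaves the treatment and crossover provisions as they are. Its cost is a less favourable stated power.

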### Recruitment {15}

All physicians at participating centers treating CSDH patients will be aware of the study so that every CSDH patient will be considered for inclusion in the study. During a kick-off meeting, clinical investigators and study support staff at each study center will be trained in communication with potential study participants and their relatives, documentation, including screening protocols, and standard operating procedures established for study purposes. Potential study participants will be recruited through conference presentations and journal articles.

## Assignment of interventions: allocation

### Sequence generation {16a}, concealment mechanism {16b}, and implementation {16c}

After the neurosurgeon has checked the inclusion and exclusion criteria, the participants are assigned to treatment with tranexamic acid or embolization in a 1:1 ratio in each study center by means of block randomization after they have given their informed consent and the baseline data have been recorded.

If, in the course of the randomized group allocation, it will be apparent that there are exclusion criteria for inclusion in the test group in the sense of contraindications for the administration of tranexamic acid, or if it will be determine during the procedure that vascular anomalies prevent embolization in patients randomized to the control group, a crossover to the corresponding comparison group is possible after prior further clarification.

